### Setting, recruitment, and sample

2.1.

This ongoing study is conducted at the University Hospital Essen, University of Duisburg-Essen, Germany, as part of the Collaborative Research Center (CRC) 289 “Treatment Expectation”, funded by the German Research Foundation (Deutsche Forschungsgemeinschaft, DFG). The overall goal of the CRC is to elucidate mechanisms and clinical implications of treatment expectations.^1^ Within the ongoing first funding phase (7/2020–6/2024), research goals are primarily focused on health outcomes relevant to patients with chronic pain and depression. The present study is accomplished as part of subproject A04 (PI: author [name]), which addresses expectancy effects on pain with a unique focus on visceral pain and conditions involving the gut-brain axis. Ethical approval for research within subproject A04, including the present experimental study, was obtained from the ethics committee at University Hospital Essen (19-8897-BO). The study has been registered in the German Registry for Clinical Studies (DRKS: DRKS00024410). All participants sign consent (for details on two versions of consent forms, see section 2.4.3), and receive a financial compensation for their participation, comprising the two study days involving pain testing described herein, as well as additional assessments accomplished as part of the CRC’s central projects (see section 2.5.7).

The recruitment goal is to include a total of *N* = 120 healthy participants in the study. The sample size is based on *a priori* power analysis with G*Power (42) for interaction effects in a repeated measure ANOVA with the factors time and group. Assuming an effect size of *d* = 0.4 for interaction effects, *α* = 0.05, and 1-β = 0.90, the number of volunteers is *N* = 96. To account for possible exclusions or drop-out and to allow stratified recruitment of male and female volunteers, a group size of *N* = 30 subjects per final experimental group is intended.

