As primary outcomes, changes in perceived pain intensity and pain unpleasantness will be assessed based on testing for interaction effects and planned group comparisons regarding changes from *Baseline* to the *Test-1 Phase* within each pain modality (study aims 2 and 3). Group differences between pain modalities will be tested based on analysis of delta scores (i.e., changes in visceral > somatic pain responses) (aim 4). Secondary pain-related outcome measures, also tested based on changes from *Baseline* to the *Test-1 Phase* within and between pain modalities, include pain-related expectations (study aim 1), pain recall, and desire to avoid pain. Secondary outcomes related to fear and stress are measured using behavioral, neuroendocrine, and psychophysiological responses, relevant particularly to study aim 6. Responses to pain-predictive cues, i.e., change in cue valence rating and in skin conductance responses, are tested for each pain modality and based on the same experimental phases as for pain-related measures. For neuroendocrine measures, we plan to compare groups with respect to changes from Baseline to subsequent sampling time points. Similarly, group comparisons of differences in heart rate variability and electrogastrogram will be based on analyses of the entire pain stimulation phases (for details, see section 2.4.2). Please note that analyses are planned in two separate steps. Initially, analyses of results of study day 1 will be accomplished. In a second step, analyses comparing data from study day 1 and day 2 (i.e., *Test-1 Phase* vs. *Test-2 Phase*) will be accomplished to explore the possible persistence of nocebo effects over time upon re-exposure to pain stimuli 1 week later (study aim 5). Mediation analyses will be accomplished for aim 1.

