### Analyses and anticipated results

3.1.

Based on the background and specific aims, we expect the following results based on planned hypotheses-testing as well as on hypothesis-generating analyses of data collected within the NoVis study, analyzed using analysis of variance (ANOVA) and t-tests as primary analysis approach. A symbolic depiction of the expected group differences in the magnitude of nocebo effects in the four experimental groups is provided in Figure 4.

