#### Aim 5: to assess the persistence of nocebo effects on responses evoked by a re-exposure to pain stimuli 1 week later

3.1.5.

We expect sustained effects of expectancy manipulations accomplished on study day 1, which we interrogate based on group comparisons of the *Test-2 Phase*, as well as based on analyses of change scores from the *Test-1* Phase to the *Test-2 Phase*. We anticipate that groups with negative instructions and/or negative experience will expect greater pain on study day 2, i.e., prior to the *Test-2 Phase*, even though elements of the treatment context, such as an i.v. line, will not be present on that day. If we indeed can show such effects, this would be an important finding toward explaining how nocebo effects may be maintained in clinical reality over time and repeated symptom experiences. Given our considerations about differences between pain modalities, especially the putatively greater psychological modulation of visceral pain, we expect sustained effects to be enhanced for the visceral pain modality. We will focus on elucidating modality-specific facets of pain recall, aiming to further elucidate the notion of a memory bias for visceral pain, expanding on our previous work (84) and the notion that visceral pain-related fear memories may be particularly resistant to extinction (41).

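### The Aim 5 persistence contrasts use only participants who return for day 2, and are biased if return depends on day-1 pain that differs by group

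*Protocol article*

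**What the plan says.** **Sample size (section 2.1).** The calculation is "for interaction effects in a repeated measure ANOVA with the factors time and group", with the input "Assuming an effect size of *d* = 0.4 for interaction effects", alpha 0.05 and power 0.90, giving 96. The target is then set at 120: "To account for possible exclusions or drop-out and to allow stratified recruitment of male and female volunteers, a group size of" 30 is intended. No drop-out rate is stated, either overall or between the two study days.

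**Method (section 3.1).** Data are to be "analyzed using analysis of variance (ANOVA) and t-tests as primary analysis approach".

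**Persistence (Aim 5).** Section 2.2 plans two steps: day-1 results first, then "analyses comparing data from study day 1 and day 2". It describes the second step as exploring persistence. Section 3.1.5 fixes two contrasts: groups compared at Test-2, and change scores from Test-1 to Test-2. It also makes a prediction: "We anticipate that groups with negative instructions and/or negative experience will expect greater pain on study day 2".

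**What happens on day 1.** In two of the four groups, heat in the Experience Phase is raised to a level calibrated to VAS 80 mm (sections 2.4.1 and 2.4.4). Section 3.1.2 predicts that Test-1 pain will differ by group. Test-2 is a separate visit a week later with 12 more painful stimuli.

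**The concern.** A t-test or ANOVA on Test-2 ratings, or on change scores that include Test-2, can use only people who have a Test-2 rating. A non-returner drops out of both Aim 5 contrasts, although their day-1 ratings were recorded a week earlier and are likely to predict what Test-2 would have been.

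This is harmless if loss is random. It is also harmless if the groups do not differ in day-1 pain and follow the same return rule. The design aims to make day-1 pain differ by group, and section 3.1.5 expects the manipulated groups to anticipate more pain on day 2. If people in more pain are less likely to come back, the manipulated groups lose more of their high scorers.

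The two contrasts can then mislead in opposite senses. A Test-2 difference that is too small understates persistence. A Test-1 to Test-2 decline that is too small overstates it.

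**Working it through.** **1. The plan's own figure.** Take f = d/2 = 0.2, k = 4 groups, and assume m = 2 measurements with correlation ρ = 0.5 (neither is stated). Then λ = f²·N·m/(1 − ρ) = 0.04 × 96 × 2 / 0.5 = 15.36 on (k − 1)(m − 1) = 3 and (N − k)(m − 1) = 92 degrees of freedom. Power is 0.912, so N = 96 reproduces. At N = 120 it is 0.964.

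**2. What the reserve implies.** 120 − 96 = 24, and 24/120 = 20%. This is the largest total loss that still leaves 96. It is shared between exclusions, drop-out and sex-stratified recruitment, so it is not a forecast of day-2 loss.

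**3. Inputs for the bias check (all assumed).** Neg-Neg against Con-Con. Rating SD 8 mm at Baseline and 15 mm at the test phases. Correlations 0.5 (Baseline with either test phase) and 0.7 (Test-1 with Test-2). True group difference +12 mm at Test-1 and +8 mm at Test-2, so a true change of −4 mm. Loss is averaged over the two groups.

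**4. Return depends on Test-1 pain.** The log-odds of non-return rise by 1.1 to 1.6 per SD, by the same rule in both groups. Large-sample results:

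| Loss | Test-2 difference, completers (true 8) | Test-1 to Test-2 change, completers (true −4) |
|---|---|---|
| 5% | 7.4 to 7.6 mm | −3.7 to −3.8 mm |
| 20% | 6.4 to 7.0 mm | −3.3 to −3.5 mm |

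The likelihood estimate that keeps non-returners' day-1 ratings gives 8.0 and −4.0 throughout.

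The two columns are linked. With equal SDs and ρ = 0.7, the bias at Test-2 is 0.7 times the bias at Test-1, so the bias in change is −0.3 times the bias at Test-1. Worst case in the table: 6.39 − 8 = −1.61 at Test-2; −1.61/0.7 = −2.30 at Test-1; change −4 + 0.3 × 2.30 = −3.31.

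**5. Return depends on Experience-Phase pain instead.** Further assumptions: +25 mm in Neg-Neg in that phase, SD 15 mm, correlation 0.5 to 0.6 with both test phases, log-odds 1.1 per SD, loss 5% to 20%.
- Completers: Test-2 difference 6.2 to 7.5 mm, but change −4.0 mm. Selection shifts Test-1 and Test-2 equally, so it cancels in the change.
- Mixed model on Baseline, Test-1 and Test-2 only: Test-2 difference 7.5 to 7.9 mm, change −4.1 to −4.5 mm. The first improves and the second gets worse.
- The same model with Experience-Phase ratings added: 8.0 and −4.0 mm.

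**6. Against sampling error.** With nobody lost, the standard error of the Test-2 difference at 30 per group is 15 × √(2/30) = 3.87 mm. At 20% loss in step 4 the bias is 1.0 to 1.6 mm, or 0.27 to 0.42 standard errors. At 5% loss it is 0.4 to 0.6 mm, or 0.10 to 0.16.

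**7. Wider range, in SD units.** With losses of 10–20%, correlations of 0.5–0.7 and Test-1 differences of 0.4–0.8 SD, logistic dependence of 1 log-odds per SD gives a Test-2 bias of −0.01 to −0.06 SD. If exactly the most painful 10–20% stay away, it is −0.06 to −0.22 SD. In one of these cases a true 0.40 SD is estimated as 0.18.

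**The case against.** **Missing-data handling may be in an analysis plan that is not shown.** This stands as far as it goes: silence on imputation or sensitivity analyses is no finding. The point here is the stated choice of method and of the two contrasts, which by construction use returners only.

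**Aim 5 is exploratory and comes second.** This stands. Section 2.2 says so, and the primary outcomes (Baseline to Test-1) are measured entirely on day 1. Still, Aim 5 is one of six specific aims, carries a directional prediction, and section 3.2 lists the day-2 re-exposure as a strength.

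**Pain-dependent return is conjecture.** Volunteers are healthy, screened and paid for both days. This stands: the documents cannot show that return depends on pain.

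**A three-phase mixed model can make one contrast worse.** This stands (step 5), and is why the fix includes the Experience Phase.

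**A reader might infer that the plan expects 20% to miss day 2.** The text does not support this. It gives no rate, the 24 places serve three purposes, and exclusions before or during day 1 are not day-2 loss.

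**A reader might also infer that any dependence of return on day-1 pain biases both contrasts.** It does not. Without a group difference in day-1 pain or in the return rule the bias is zero, and under step 5 the change contrast is unbiased among completers.

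**Conclusion.** The concern holds in conditional form. The stated Aim 5 contrasts exclude non-returners. If return depends on day-1 pain and that pain differs by group, the Test-2 difference is biased towards zero. If return depends on Test-1 pain specifically, the Test-1 to Test-2 decline is understated as well.

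Under the assumptions of steps 3 and 4, a true 8 mm becomes 7.4–7.6 mm at 5% loss and 6.4–7.0 mm at 20%. That is modest against the standard error, though sharper selection could make it material. Every input to the bias figures is assumed, because the article reports neither a day-2 loss rate nor rating variances. The primary analyses and the sample size of 96 are not in question. The change is worth making because a better method is available at almost no cost.

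**What to change.** For Aim 5, replace the ANOVA and t-tests by one linear mixed model per outcome and pain modality:
- Fit it to all randomised participants with any day-1 rating.
- Use group × phase, sex, and an unstructured within-person covariance.
- Include Baseline, Experience, Test-1 and Test-2 ratings. For visceral outcomes, add the thermal Experience-Phase rating as an auxiliary outcome, since that is where the manipulation acts. Section 2.5.3 has ratings collected in all pain stimulation phases.
- Take the Test-2 group contrasts and the Test-1 to Test-2 contrasts from this model.
- Report non-return by arm.

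Cost: somewhat more modelling work, with no extra data or participants. The model removes the bias only if return depends on recorded ratings. With complete data its contrasts differ trivially from the ANOVA if sex is not exactly balanced across groups.

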Building on long-standing knowledge on the role of nocebo mechanisms in the generation and worsening of nausea [reviewed in (1)], our group started experimental work to systematically study both placebo and nocebo effects in visceral pain and fecal urgency induced by rectal distension [reviewed in (27)]. Together, data from behavioral and neuroimaging studies in healthy volunteers as well as in patients with IBS and IBD support that treatment expectations effectively change the subjective response to objectively identical painful visceral stimuli in healthy individuals, inducing placebo analgesia or nocebo hyperalgesia, along with changes in neural activation in key brain regions (32–34) known to be involved in the processing of visceral pain (35). While this research focused primarily on positive treatment expectations underlying placebo effects, we also initiated work elucidating the effects of negative treatment expectations, employing negative treatment suggestions and (thus far to a much smaller extent) learning/conditioning procedures to induce negative expectations underlying nocebo effects. Providing specific written and verbal treatment information or creating distinct treatment experiences through learning/conditioning procedures constitute the two paradigms which have been implemented in order to experimentally generate and explore both placebo and nocebo effects in laboratory settings (36, 37). The distinction between “instruction” and “experience/conditioning” as principle psychological mechanisms has been the basis for different experimental study designs, although it is becoming increasingly clear that these processes are conceptually and clinically intertwined (27). Clearly, prior experience and learning processes shape and interact with treatment instruction within any given clinical or experimental context, giving rise to expectancies (38). The combination of instruction and experience has been shown to be particularly effective in eliciting a nocebo effect (39), but this has never been tested in the context of visceral pain. The putative relevance of stress-related state factors like anxiety, fear, and stress also remains unclear in the context of nocebo effects but is strongly supported by our study showing that acute psychosocial stress amplified visceral nocebo effects in healthy individuals (40). Given that visceral pain sensitivity is demonstrably more responsive to the acute stress mediator cortisol (31) and uniquely driven by pain-related fear (29) it is intriguing to speculate that nocebo effects may be more pronounced for sensations arising from the visceral modality, as interoceptive sensations, when compared to exteroceptive sensations like thermal cutaneous pain. The notion of more “powerful” visceral pain modulation by mechanisms engaged during nocebo responses is also of interest given altered visceral pain-related fear learning in IBS (28) as well as greater emotional and hypothalamic–pituitary–adrenal (HPA) axis stress responsivity in patients with IBS and IBD (10). Therefore, elucidating the role of fear, anxiety, and stress in the context of nocebo research is a timely and important goal of our experimental study concept and design.

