To this end, healthy men and women between 18 and 45 years of age and a body mass index between 18 and 30 are recruited for a study on visceral vs. somatic pain perception by public advertisement in the surrounding universities, clinics, and community of the Ruhr area. The standardized recruitment and screening process consists of a structured telephone screening and a personal interview. Exclusion criteria include any acute or chronic health condition, with particular attention to recurring pain and frequent gastrointestinal symptoms based on self-report and an established questionnaire assessing various symptoms over the past 3 months (43), regular use of medications (except contraceptives and thyroid medication), elevated anxiety and depression scores based on the Hospital Anxiety and Depression Scale (HADS) (44)(subscale scores ≥8 used as cut-offs), pregnancy or breastfeeding (urinary pregnancy test on the first day of the study), and insufficient proficiency in the German language. A physical examination including a digital rectal examination is performed to exclude external or internal anorectal tissue damage which may interfere with rectal balloon placement. Given standardized brain scanning protocols accomplished as part of a CRC central project, the standard magnetic resonance imaging (MRI)-related exclusion criteria apply (e.g., metal implants, pacemaker, large tattoo in head/neck position, and known claustrophobia), and structural brain abnormalities are excluded in collaboration with the Institute of Diagnostic and Interventional Radiology and Neuroradiology. Given the study aims, especially the putative role of prior experiences with the experimental paradigms, any participation in an experimental pain study involving somatic or visceral pain stimuli within the previous 3 months (based on self-report) is also exclusionary.

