#### Treatment instruction

2.4.3.

During the initial recruitment and screening stages, accomplished by study staff prior to randomization, all participants are only informed that the purpose of the study is to evaluate mechanisms of visceral when compared to somatic pain perception. Of note, the general information provided on study-related materials (e.g., study flyers) and during phone screening does not contain any reference to the possibility of receiving a pronociceptive drug or a placebo, but rather focusses on dynamic changes in pain perception upon repeated painful experiences and underlying psychobiological mechanisms. Randomization is accomplished prior to the personal interview with the study physician (for details, see section 2.4.5). Depending on treatment instruction group, participants then receive distinct written and verbal treatment information, and sign distinct versions of consent forms. All treatment-related information is provided by the study physician (author [name]) based on a highly standardized protocol at various time points of procedures, illustrated in Figure 2. For negative instruction groups, the protocol is built on a previously used approach to generate negative expectations about expected pain increase induced by treatment suggestions regarding an intravenous infusion of the opioid antagonist Naloxone (in reality: always saline) [e.g., (40)]. Herein, participants give consent to participating in a placebo-controlled, double-blind study implementing the opioid antagonist Naloxone vs. saline to study pain sensitization and pain responses during an amplified pain experience in two modalities, with a 1:1 randomization ratio (*consent form version A*). Of note, saline is always administered, hence the procedures involve a deception with respect to the randomization ratio and the possibility to receive naloxone (for a critical discussion, please see section 3.2). The briefing contains detailed information about the drug, especially about its pain-enhancing effects, but also about typical clinical uses and known side effects. The “study drug,” which has an official design of the pharmacy of the University Hospital Essen, is placed directly in front of the subject before administration into the i.v. line. In instruction control groups, written and verbal information about the administration of saline is provided (*consent form version B*). The rationale for the study is also adjusted, focusing only on differences between pain modalities. Regarding the i.v. infusion of saline, volunteers are told that it is simply part of standardized procedures. In the context of placing the i.v. line and starting the saline drip, the study physician emphasizes that no active substance is given. Note that perceived treatment allocation is assessed with a questionnaire at the end of study day 2 in all participants and groups. Volunteers randomized to consent form version A, i.e., negative instruction groups, will at the end of the study be fully informed regarding the administration of saline in all participants. The rationale for the deception regarding the possibility of receiving Naloxone will be provided, and participants will be offered the opportunity to withdraw their study data.

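### The 3-month look-back for earlier pain studies does not screen out volunteers who may know the group's naloxone/saline deception, which could weaken the negative instruction

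*Protocol article*

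**What the plan says.** The listed criteria in section 2.1 contain one rule on earlier studies: "any participation in an experimental pain study involving somatic or visceral pain stimuli within the previous 3 months (based on self-report) is also exclusionary". The reason given is "Given the study aims, especially the putative role of prior experiences with the experimental paradigms". Volunteers are recruited locally, "by public advertisement in the surrounding universities, clinics, and community of the Ruhr area".

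Section 2.4.3 explains where the negative instruction comes from: "the protocol is built on a previously used approach to generate negative expectations about expected pain increase induced by treatment suggestions", these suggestions being "regarding an intravenous infusion of the opioid antagonist Naloxone (in reality: always saline". It cites reference 40 as an example. The Introduction describes that reference as "our study showing that acute psychosocial stress amplified visceral nocebo effects in healthy individuals (40". The same group has therefore already used this cover story in the same kind of volunteer.

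Section 2.4.3 also says that participants given the negative instruction in the present study "will at the end of the study be fully informed regarding the administration of saline in all participants". Perceived allocation is asked of everyone at the end of study day 2.

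**The concern.** The rule treats earlier participation as an exposure that fades. That is reasonable for pain experience. Learning that an infusion presented as naloxone was saline is different: a person who learned it a year ago still knows it. Under the listed criteria that person becomes eligible three months after the earlier study. The rule also asks only about pain stimuli, not about the feature of the earlier study that matters here.

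Elsewhere the protocol takes care to keep volunteers naive. According to section 2.4.3, flyers and telephone screening are silent on any pain-enhancing drug or placebo. The eligibility rule leaves a gap in that protection.

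The consequence falls mainly on two arms. Someone who suspects saline has less reason to expect more pain under consent form A, and less reason to read the hotter stimuli of the Experience Phase as proof of having received naloxone. Section 3.1.1 offers that attribution as one possible route to a visceral nocebo effect. The control-instruction arms are truthfully told that they receive saline, so they have no corresponding manipulation to lose. The instruction effect in Aim 2 would shrink, and so would its combination with experience in Aim 3, which section 3.1.3 calls the most crucial aspect of the study.

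**Working it through.** **Step 1: can such a person enter?** The documents support these links:
- the bar lasts 3 months and rests on self-report (2.1);
- the cover story was used before (2.4.3);
- it was used by the same group in healthy individuals (Introduction);
- no other listed criterion addresses it (2.1).

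Two links are not documented: that the earlier volunteers were debriefed (assumed from the practice described for this study), and that any of them re-enrolled.

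**Step 2: reproduce the planned sample size.** Inputs from section 2.1: d = 0.4 for the time-by-group interaction, α = 0.05, power 0.90, N = 96. From the design: k = 4 groups and m = 2 phases (Baseline, Test-1). Assumed, because not stated: correlation ρ = 0.5 between phases.

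- f = d/2 = 0.2
- λ = f² × N × m/(1 − ρ) = 0.04 × 96 × 2/0.5 = 15.36
- df1 = (k − 1)(m − 1) = 3; df2 = (N − k)(m − 1) = 92
- power from the noncentral F distribution = 0.9115

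With N = 92 the power is 0.898, so 96 is the smallest total with equal groups that reaches 0.90. The stated figure is reproduced. With all 120 analysed, λ = 0.04 × 120 × 4 = 19.2 and power is 0.964.

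**Step 3: dilute the effect.** Let q be the share of the 60 negative-instruction participants in whom the instruction does nothing. The documents give no value for q, so a range is shown. As a worst case the whole interaction effect is scaled: d becomes 0.4(1 − q), and λ is multiplied by (1 − q)².

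| q | Number of 60 | d | (1 − q)² | Power, N = 120 | Power, N = 96 | N for 90% power |
|---|---|---|---|---|---|---|
| 0 | 0 | 0.40 | 1.00 | 0.964 | 0.912 | 96 |
| 5% | 3 | 0.38 | 0.90 | 0.945 | 0.878 | 104 |
| 10% | 6 | 0.36 | 0.81 | 0.918 | 0.838 | 116 |
| 20% | 12 | 0.32 | 0.64 | 0.836 | 0.733 | 144 |

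If all 120 are analysed, power stays above 0.90 up to 10% affected and is 0.882 at 15%. If only 96 are analysed, 2% affected already gives 0.899. Section 2.1 explains the step from 96 to 120 by exclusions, drop-out and stratification by sex, so it is not reserved for this kind of dilution.

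**Step 4: why this is a worst case.** The d = 0.4 belongs to the overall time-by-group interaction, not to the instruction effect. Part of that interaction comes from the experience manipulation alone, which does not depend on belief in naloxone and would not shrink. A previously deceived person may also still respond in part to the instruction.

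**The case against.** A reader might infer that the trial is enrolling people who have been told the secret, and that the instruction cannot work in them. The documents do not support either statement. Debriefing is described only for the present study, and nothing shows that anyone re-enrolled. A past participant could still believe that a new study, with its own consent form, stated 1:1 allocation and pharmacy-labelled drug, does use naloxone. Nor does visceral generalisation depend only on drug attribution: section 3.1.1 calls that a possible cause, and section 3.1.2 allows for generalisation as well as attribution. A reader might also infer biased allocation. Randomisation spreads such volunteers over all four arms, so a share of 20% would mean about 24 of 120 enrolled, which would be many for a publicly advertised study. These limits stand.

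It can also be said that the article condenses a fuller protocol, that its list of exclusions may not be complete, and that the content of the telephone screen is not shown. That would answer a complaint about a missing detail. Here, however, the article states the rule, its window and its reason, and the window does not fit knowledge of a deception.

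Finally, the protocol has manipulation checks: G-EEE ratings around the infusion, expected-pain ratings before each phase, mediation analyses for Aim 1 and the perceived-allocation question. These can reveal a weak induction but cannot prevent one. Excluding participants on the strength of them would be selection after randomisation.

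The objection that a telephone question about placebo or deception could itself raise suspicion is sound, and it shapes the fix.

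**Conclusion.** The point holds in a limited form. The 3-month, self-reported rule is not suited to keeping out volunteers who know the naloxone/saline deception from the group's earlier work. If any enrol, the likely result is attenuation of the instruction effect and of its interaction with experience, with lost power. It does not create imbalance between groups, and the direction is towards the null.

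The size is unknown. At a few per cent affected with all 120 analysed, the loss is small (worst-case power 0.945 at 5%). It becomes material at 20% (0.836), or if attrition brings the analysed number down to 96 (0.878 at 5%, 0.733 at 20%). These figures rest on ρ = 0.5, on an assumed share, on assumed earlier debriefing, and on scaling the whole interaction effect. The change is worth making because it is cheap and the study is still recruiting, not because harm has been shown.

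**What to change.** In section 2.1, keep the 3-month rule for exposure to pain stimuli. Add an exclusion without time limit for anyone who has taken part in a study of this group that used a deceptive drug instruction.

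Apply it before randomisation in two parts. First, ask a neutral question at screening, for instance whether the person has ever taken part in a study of this group, with no mention of a drug, placebo or deception. Second, check the answer against the group's own participant records, where these may be used, to identify which study it was.

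For participants already enrolled, run the same record check blind to group. Then repeat the Aim 2 and Aim 3 analyses as a sensitivity analysis that leaves such participants out of all four arms. Earlier participation is fixed before randomisation, so this keeps the comparison randomised.

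The cost is one screening question, a record check, a short amendment and the loss of a few otherwise eligible volunteers.
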